**Fig. 2 Fig2:**
[figure not shown]
ICE-COVID trial design. The flow chart summarises the design of the ICE-COVID trial

### Study setting

The study will be conducted at Swansea Bay University Health Board, Swansea, UK.

### Recruitment/consent

Potentially eligible participants will be identified via posters, social media and local and national press. Interested participants will be able to self-identify by contacting the research team via the research email address or study telephone. In reply, they will be given a sequential screening ID and sent an online screening questionnaire to assess their eligibility against inclusion and exclusion criteria outlined in Fig. 3 and ensure participants agree to refrain from taking disallowed medication during the trial period (Table 1). They will be entered into the screening log, on the REDCap™ database hosted by Swansea Trials Unit (https://redcap.swansea.ac.uk/), where exclusions can be documented. The screening tool will be administered electronically to minimise contact during the COVID-19 pandemic. This electronic form will be assessed by the trial team to determine eligibility for the trial.

**Fig. 3 Fig3:**
[figure not shown]
ICE-COVID inclusion and exclusion criteria

**Table 1 Tab1:** Disallowed medication during the trial period

**Disallowed co-medication**	
Antihistamines Decongestants Antitussives Combination cold products Antivirals Oral or nasal steroids All nasal sprays	

Eligible participants will be emailed the information sheet and consent form to read in advance of their face-to-face enrolment visit. Written, informed consent to participate will be obtained from all participants. During all face-to-face appointments, the recommended government guidelines will be followed on social distancing and personal protective equipment for both the research team and participants. Informed consent will be undertaken by a Good Clinical Practice (GCP) trained research nurse and recorded on the REDCap™ database prior to the participant undergoing procedures that are specifically for the purposes of the study.

### Randomisation

Following consent, baseline data will be collected, and the participants will be issued a randomisation ID which will assign them to either placebo or verum spray. This will be documented on the enrolment log. The randomised spray bottles will be stored at Swansea University, UK, for assignment to subject participants.

Randomisation sequence will be created using R 3.6.3 (R Core Team 2020) based on the pseudorandom number generation algorithm “Mersenne-Twister” using a 10-digit seed for reproduction. Participants will be assigned to the respective treatment with a 1:1 allocation and fixed block size by a statistician with no clinical involvement in the trial.

### Blinding

Blinding will occur at the site of manufacture of spray bottles, which will be assigned a randomisation number. Both the study investigators and participants will be blinded to the type of spray bottle being used. Numbered sealed blinding envelopes will be kept in Swansea University, which will only be opened if there is a severe adverse reaction to determine if the study participant received verum or placebo.

### Treatment arms/intervention

Participants will be randomly allocated to each of either the treatment arm (verum Coldamaris plus, 1 ml of the solution containing 1.2 mg iota-carrageenan (Carragelose®), 0.4 mg kappa-carrageenan, 0.5% sodium chloride and purified water) or placebo (Coldamaris sine, saline 0.5%) arm. Coldamaris plus is a CE marked device Directive 2001/20 and GMP-Directive 2003/94/EC. Participants will be instructed to administer the spray prophylactically into each nostril and throat 1 puff three times a day (TDS) according to the manufacturer’s instructions and will be asked to continue even if symptoms develop. The trial will run for a total of 8 weeks per participant, during which time the participants will be invited to complete a daily symptom tracker.

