Carrageenan covers a range of sulphated polysaccharides and oligosaccharides extracted from red edible seaweed. It is widely used to thicken, emulsify, and preserve food and drink, as a vegetarian and vegan alternative to gelatin, as well as in the cosmetic and pharmaceutical industry. The three commercially important carrageenans are iota-, kappa- and lambda- carrageenans, which consist of disaccharide repeating units with one, two and three sulphate ester groups respectively [20]. The in vitro antiviral activity of carrageenan was first described in 1958 when carrageenan was shown to exert a marked inhibitory effect on the growth of influenza B virus and mumps virus in embryonated chicken eggs [21]. Since then, carrageenan has shown in vitro anti-viral efficacy against a wide range of viruses [22–32]. Recently, it has been demonstrated to have in vitro antiviral activity against the novel SARS-CoV-2 [33]. In vivo clinical trial data has previously demonstrated the benefit of iota-carrageenan nasal spray in reducing the duration of symptoms of the common cold, as well as the viral load in nasal lavage, compared with saline placebo sprays [34–38]. The mechanism of action is believed to be one of preventing the binding and entry of viral particles into nasal epithelial cells [22]. In order to cause infection respiratory viruses must reach their specific host cell surface receptor by moving through respiratory fluid and mucus (10 μm depth) without any means of self-propulsion [39]. Initially, this depends on Brownian motion and eventually the positively charged virus comes close enough to the cell to be attracted via large negatively charged molecules on the cell surface known as Heparan Sulphate (HS) Proteoglycans [40]. It is thought that Carrageenan mimics the HS and can, therefore, trap the virus and prevent infection of adjacent epithelial cells [35]. Carrageenan trapped viruses are thought to be transported by mucociliary clearance to the nasopharynx, swallowed, and then destroyed in stomach acid.

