#### Baseline assessment

Participant demographics including date of birth, gender and ethnicity will be recorded. Medical history will be recorded including current medical conditions, regular medications, and any allergies. Participants will be asked to complete a quality-of-life questionnaire: EQ-5D-3L, this will also allow for a later cost-effectiveness analysis as well as undergo the baseline blood tests outlined above. Randomisation and training in spray application will take place after baseline assessments and questionnaires have been completed, on the same day.

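### Fixed block size and a PCR-only primary analysis leave the trial more exposed than it need be if the carrageenan spray can be told from saline

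*Protocol article*

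**What the plan says.** **Products.** Under Treatment arms/intervention, 1 ml of the active solution contains "1.2 mg iota-carrageenan (Carragelose®), 0.4 mg kappa-carrageenan, 0.5% sodium chloride and purified water". The comparator is the "placebo (Coldamaris sine, saline 0.5%) arm". Of carrageenan in general, the Introduction says: "It is widely used to thicken, emulsify, and preserve food and drink". Participants spray each nostril and the throat three times a day for 8 weeks.

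**Blinding.** The Blinding section says: "Blinding will occur at the site of manufacture of spray bottles, which will be assigned a randomisation number", and "Both the study investigators and participants will be blinded to the type of spray bottle being used". Sealed envelopes are opened only after a severe adverse reaction. The trial design section extends blinding to allocation, administration and data analysis.

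**Allocation.** The Randomisation section says: "Participants will be assigned to the respective treatment with a 1:1 allocation and fixed block size", with a statistician who has no clinical involvement responsible. The block size is not given. The trial is single-centre. On the timing of allocation, Baseline assessment says: "Randomisation and training in spray application will take place after baseline assessments and questionnaires have been completed, on the same day".

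**Primary outcome.** The Abstract and the Outcomes section define it as a positive PCR swab taken at symptom onset, or seroconversion. The Seroconversion section has antibodies measured in participants at start and end, and calls this essential for finding asymptomatic infection. Under Statistical analysis, however, the primary outcome is described as a binary variable for confirmation by PCR swab or not, with no mention of serology.

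**The concern.** A participant who uses a spray many times over 8 weeks, or a nurse who teaches its use, might notice a difference if one product contains a thickener and the other does not. Two consequences should be kept apart.

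The first concerns allocation concealment. With a constant block size at one centre, anyone who knows that size and can identify earlier allocations knows for certain what the remaining places in some blocks must be. That could influence who is enrolled next. It does not bias how participants report symptoms.

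The second concerns ascertainment. A PCR result exists only if a participant reports symptoms and is swabbed. If those who believe they are on active spray report or swab less, fewer infections are found in that arm and a null product can look protective. Serology taken from everyone does not depend on reporting, so an analysis that leaves it out discards the component least open to this bias.

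**Working it through.** **1. The plan's own sample size.** Inputs from the sample size section: event rates 25% and 12.5%, two-sided 5%, power 80%. With pooled variance under the null (mean rate 0.1875) and no continuity correction:

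n = [1.960·√(2·0.1875·0.8125) + 0.842·√(0.25·0.75 + 0.125·0.875)]² / 0.125² = 151.9, so 152 per arm and 304 in total. Power at 152 is 80.03%. Allowing for 20% loss, 304/0.8 = 380. The stated figures reproduce, and this point does not change them.

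**2. Composition.** 1.2 + 0.4 = 1.6 mg carrageenan per ml, or 0.16% w/v, in the active spray, and none stated in the placebo. Both contain 0.5% sodium chloride. The article gives no figure for viscosity, taste or feel, so the chance of recognition cannot be calculated.

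**3. Fixed blocks.** Assume that the block size is known and every earlier allocation has been identified. Enumerating all balanced 1:1 blocks, the share of allocations known with certainty beforehand is:

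| Block size | Share certain |
|---|---|
| 2 | 1/2 = 50% |
| 4 | 1/3 = 33% |
| 6 | 1/4 = 25% |
| 8 | 1/5 = 20% |

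For size 4 there are 6 possible blocks holding 24 allocations, of which 8 are forced: 8/24 = 1/3. If no allocation is identified, the share is zero whatever the block size.

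**4. Ascertainment with no true effect.** None of these inputs is given in the documents as a parameter of this kind: 25% true infection in both arms (the higher planning rate), 60% of infections symptomatic, PCR sensitivity 90%, exit serology capturing 72% of infections independently of the swab, and swab uptake u of 90% on placebo against 80%, 70% or 50% on active.

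- PCR only: risk = 0.25 × 0.6 × u × 0.9
- PCR or seroconversion: risk = 0.25 × [1 − (1 − 0.6 × u × 0.9) × (1 − 0.72)]

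On placebo (u = 0.9): PCR only = 0.25 × 0.486 = 12.2%. PCR or seroconversion = 0.25 × (1 − 0.514 × 0.28) = 21.4%.

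The type I error is the two-sided rejection rate of the two-proportion z-test at 152 per arm: Φ[(d − 1.96·SE₀)/SE₁] + Φ[(−d − 1.96·SE₀)/SE₁]. Here d is the difference in detected risk, and SE₀ and SE₁ are the pooled and unpooled standard errors.

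| Active-arm uptake | PCR only, active | Bias (points) | Type I error | PCR or seroconversion, active | Bias (points) | Type I error |
|---|---|---|---|---|---|---|
| 80% | 10.8% | 1.4 | 6.6% | 21.0% | 0.4 | 5.1% |
| 70% | 9.5% | 2.7 | 12% | 20.6% | 0.8 | 5.3% |
| 50% | 6.8% | 5.4 | 36% | 19.9% | 1.5 | 6.2% |

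Seroconversion alone has a detected risk of 0.25 × 0.72 = 18.0% in both arms at every uptake, so it carries no bias from swabbing under these assumptions.

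**The case against.** The strongest reply is that nothing in the article says the sprays can be told apart. Thickening food and drink is not evidence about the feel of a 0.16% spray. Sensory matching is also the kind of detail that a condensed article leaves to the full protocol, which the article says is available on the registry. The Introduction cites earlier carrageenan trials against saline sprays, so the comparator follows precedent. All of this stands, and silence on matching is not counted here as a fault.

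A reader might infer that blinding is secured only by the bottle and its number. The documents do not support that. Administration and data analysis are also declared blinded, allocation is by a statistician with no clinical role, and code breaks are in sealed envelopes.

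A reader might also infer that the double-blind claim, and with it every self-reported result, cannot be defended, or that fixed blocks bias self-report. Neither follows. Recognition is not shown, the secondary analyses are declared mainly exploratory, and predictable blocks threaten concealment rather than reporting. Participants spray themselves, so staff may never experience the product, and nothing says that site staff know the block size.

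Finally, the primary outcome as defined is laboratory-based and well protected by serology in everyone. That is correct, and it is the reason to analyse the outcome as defined. The PCR-only wording may be shorthand in the article. If so, the correction costs nothing.

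**Conclusion.** The point holds as one of avoidable exposure to a possible but undocumented risk. It is not a demonstrated failure of blinding.

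- **Concealment.** A fixed block size would make a quarter to a third of allocations certain with blocks of 6 or 4, but only if the block size is known and earlier allocations are recognised or unblinded. The plan does not state the size.
- **Primary analysis.** The definition under Outcomes and the variable described under Statistical analysis disagree, and the second is the more fragile. Under the assumed inputs, type I error is about 7% to 36% for PCR alone and about 5% to 6% for PCR or seroconversion. The 36% needs the most extreme case, uptake of 50% against 90%. The direction, with fewer swabs on active, is also assumed.

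No stated figure in the plan changes.

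**What to change.** 1. **Randomisation.** Replace the fixed block size with randomly varying block sizes, and state that they are not disclosed to site staff. This is a small change to the R code that generates the sequence.
2. **Statistical analysis, primary outcome.** Define the analysed variable as positive PCR or seroconversion, to agree with the Outcomes section.
3. **Supportive analysis.** Add seroconversion alone in participants with paired sera, and tabulate swabs taken per symptomatic episode by arm. Both should use data the trial already collects, at the cost of two further tables.

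The supportive analysis is limited to participants with exit serology, so losses to follow-up reduce it. Because vaccination was being rolled out during the trial, antibodies that appear after vaccination in follow-up would need to be accounted for wherever seroconversion counts as infection.

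An item at the existing week 4 contact asking which spray participants think they have, and why, is optional. Such guesses can partly reflect perceived efficacy.

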### Outcomes

#### Primary outcome

Acquisition of COVID-19 infection as confirmed by a positive PCR swab taken at symptom onset or seroconversion during the study

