#### Seroconversion

Participants will be tested for SARS-CoV-2 antibodies using the enzyme-linked immunosorbent assay at the start and end of the study period. The presence of SARS-CoV-2 antibodies at the start of the trial indicates the previous infection with COVID-19 and the participant data will as such be excluded from the trial. Participants will be deemed to have acquired COVID-19 during the study period if they are antibody negative at the start of the study and positive for SARS-CoV-2 antibodies at the end of the study (i.e. seroconversion). This will be an essential means of detecting individuals with asymptomatic infection during the study period.

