### Statistical analysis

Data will be analysed in accordance with an intention-to-treat analysis. Each of the outcome measures will be checked for the distribution to be normal. Each of the outcome measures and important baseline covariates would be reported along with their missingness. If required appropriate imputation method would be adopted in the main analysis. All the statistical data management and analysis will be done under standard statistical software (e.g. STATA version 16 or IBM SPSS version 26).

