#### Primary outcome

The primary outcome measure is a binary variable whether COVID-19 infection has been confirmed by PCR swab or not. We will perform a summary analysis reporting the outcome of the categories of two trial arms with respect to the primary outcome measure. The odds ratio and related statistical significance of the chi-square test will be reported. Following on, an adjusted analysis will be done adopting a logistic regression model. The adjustment would be done using the baseline covariates like demographics, co-morbidities (especially history of COVID-19), current medications along with baseline QoLs. The selections of the covariates would be done based on literature reviews along with discussing with the clinical co-applicants involved in this trial. This will also depend on the missing of the covariates and the selection procedure in the statistical modelling.

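### The primary endpoint has two definitions: symptom-onset PCR or seroconversion under Outcomes, and PCR confirmation alone, at any time, under Statistical analysis

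*Protocol article*

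**What the plan says.** The protocol article states the primary outcome in three places.

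- **Abstract and Outcomes, Primary outcome:** COVID-19 infection "confirmed by a positive PCR swab taken at symptom onset or seroconversion during the study". The PCR limb carries a condition on when the swab was taken. Seroconversion is a second, independent limb.
- **Statistical analysis, Primary outcome:** "The primary outcome measure is a binary variable whether COVID-19 infection has been confirmed by PCR swab or not". There is no condition on timing or symptoms, and seroconversion is not mentioned.

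The Seroconversion section provides for antibody testing by "enzyme-linked immunosorbent assay at the start and end of the study period", with none in between, and says of this testing: "This will be an essential means of detecting individuals with asymptomatic infection during the study period".

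For missing data, the Statistical analysis section says: "If required appropriate imputation method would be adopted in the main analysis". The primary objective is the risk of COVID-19, with no condition on how an infection comes to light. The article does not say how a positive PCR obtained other than at symptom onset is to be scored.

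**The concern.** A primary endpoint must give each participant one status. Here two rules are in force, and each leaves out laboratory evidence that the other accepts.

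Under Outcomes, a positive PCR counts only if the swab was taken when symptoms began. Exit serology is meant to pick up the rest, but it cannot show an infection acquired too close to the exit visit for antibody to have appeared. For such a participant, a PCR done for another reason may be the only proof of infection, and the literal wording sets it aside.

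Under Statistical analysis, that PCR counts. The participant who never had symptoms, was never swabbed and seroconverted does not, although the article regards serology as essential for finding exactly these people.

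The event count, and with it the odds ratio and the chi-square test, therefore depends on which section the analyst follows. The secondary outcome on other respiratory infections is restricted to participants who are not COVID-19 positive. That term is not tied to either definition, so membership of that group is unsettled too.

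**Working it through.** **Step 1. The two definitions side by side, for evaluable participants (exit antibody result available)**

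| Participant | Outcomes definition | Analysis definition |
|---|---|---|
| Positive PCR at symptom onset, any exit antibody | case | case |
| No positive PCR, seroconverts | case | not a case |
| Positive PCR for another reason, seroconverts | case | case |
| Positive PCR for another reason, exit antibody negative | not a case | case |

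The definitions disagree in rows 2 and 4, in opposite directions, so neither one contains the other.

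**Step 2. Reproduce the planned sample size**

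Inputs from the Sample size section: risks 25% and 12.5%, two-sided 5% level, 80% power, 20% loss. The result does not depend on which arm has which risk. With mean risk 0.1875 and no continuity correction:

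n per arm = [1.960 × √(2 × 0.1875 × 0.8125) + 0.842 × √(0.25 × 0.75 + 0.125 × 0.875)]² / 0.125² = 151.9, rounded up to 152.

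The total is 304, and 304 / 0.80 = 380. Both stated totals reproduce, and power at 152 per arm is 80.0%. The sample size arithmetic is not the problem.

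**Step 3. Size of the row 4 gap**

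The article gives no figure for this, so the inputs are assumptions:

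- share of infections that are asymptomatic, a: 20% to 40%;
- share of those with a PCR for some other reason, q: 25% to 75%;
- antibody lag: 14 days of a 70-day follow-up, with infections spread evenly, so a share 14/70 = 0.20 falls too late for exit serology;
- the same share missed in both arms, and planning risks that refer to all infections.

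Share of infections proven by PCR but uncounted under the Outcomes wording: m = a × 0.20 × q.

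- Low: 0.20 × 0.20 × 0.25 = 0.01
- High: 0.40 × 0.20 × 0.75 = 0.06

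Participants lost to follow-up are left out of m, because 152 per arm is already the number remaining after the 20% loss.

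Expected events among those evaluable: 152 × 0.25 + 152 × 0.125 = 38 + 19 = 57. Uncounted: 57 × 0.01 = 0.6 to 57 × 0.06 = 3.4.

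Power at 152 per arm with both risks multiplied by (1 − m):

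| m | Risks | Power |
|---|---|---|
| 0 | 25.0% and 12.5% | 80.0% |
| 0.01 | 24.75% and 12.375% | 79.5% |
| 0.06 | 23.5% and 11.75% | about 77% |

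**Step 4. Row 2, the opposite gap**

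With the same assumed inputs, and supposing every symptomatic infection yields a positive onset swab, the share of infections known only through seroconversion is a × (1 − q) × 0.80. This runs from 0.20 × 0.25 × 0.80 = 4% to 0.40 × 0.75 × 0.80 = 24%. It is illustrative only, but it shows that settling the conflict by adopting the PCR-only wording would probably lose more events than adopting the Outcomes wording.

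**The case against.** A reader might infer that anyone with a positive PCR outside symptom onset and no positive exit antibody will be scored as uninfected. The documents do not support that.

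- **The scoring is not settled.** The only section that defines the analysed variable would count such a PCR. The non-case result follows only if the Outcomes wording controls, and the article does not say that it does.
- **A missing exit sample is not a negative one.** A participant lost before the exit blood has missing serology, and the article provides for imputation. No rule equates missing with uninfected. What remains is that imputing a status already proven by PCR would be odd, and a single definition would avoid it.
- **The other-respiratory-infection outcome is not broadly contaminated.** It is based on symptoms, so participants without symptoms cannot be counted in it.
- **The article describes no PCR testing other than at symptom onset.** The condition may simply describe when the study swab is triggered, with exit serology as the intended route for asymptomatic infection. The number affected by the row 4 gap may be small, and the full protocol, which is not shown, may say how outside results are handled.
- **Outside tests are ascertained unevenly.** They depend on job, exposure and self-report. Study-triggered swabs plus exit serology are a defensible design, and losing the same share of events in both arms leaves the test under the null valid.

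All five points stand as limits on the size and certainty of the problem. None removes the conflict, because the Outcomes and Statistical analysis sections still assign different statuses to the same participant.

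**Conclusion.** The concern holds as an inconsistency in the primary endpoint. Outcomes restricts PCR to symptom onset and adds seroconversion. Statistical analysis lifts the restriction and drops seroconversion. Neither version counts every laboratory-proven infection, and the article does not say which governs.

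The symptom-onset condition taken alone has a modest effect: about 1% to 6% of infections, or 0.6 to 3.4 of 57 expected events among evaluable participants, with power of about 79.5% to 77% instead of 80%. These figures rest wholly on the assumed asymptomatic share, outside-testing share and antibody lag. The inconsistency itself rests on no assumption. It should be corrected mainly so that the endpoint is well defined and matches the objective; the loss of power is secondary.

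**What to change.** Use one definition in the Abstract, in Outcomes and in Statistical analysis: any laboratory-confirmed positive SARS-CoV-2 PCR on a sample taken within the outcome window, whatever the reason for the test and whether or not symptoms were present, or seroconversion between the start and exit samples. State the window. Then:

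- use the same definition for COVID-19 positive in the secondary outcome on other respiratory infections;
- record the dates and results of outside tests in the existing daily tracker and at the exit visit;
- report symptom-onset PCR cases as a separate component, so that the uniformly triggered part of the endpoint stays visible.

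The cost is wording and one added question. The small downside is that outside tests depend on self-report. Participants and investigators are blinded, so reporting should not differ by known allocation.
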